### Hypotheses

#### Clinical part

We hypothesize that children with Cerebral Palsy (CP) who are treated with a knee-ankle-foot orthosis (KAFO) will show a smaller decline in (or even increase in) ankle range of motion (ROM) into dorsiflexion compared to children not being treated with a KAFO. In addition, we anticipate that children who are treated with a static KAFO will show less of a response (i.e. they will have a larger decline or a smaller increase in ankle ROM into dorsiflexion) when compared to children being treated with a dynamic KAFO.

We expect that for children with CP, treatment with either KAFO will have a less negative change in gait or even a positive change in gait pattern. A positive change refers to less ankle plantar flexion and less knee flexion in midstance, compared to no KAFO treatment. The effects are expected to be more positive in children being treated with the dynamic KAFO compared to the children being treated with the static KAFO.

The level of mobility (GMFM-score) of children who are treated with either KAFO is expected to show a smaller decline or increase compared to children who are not treated with a KAFO. As above, the effects are expected to be larger in children being treated with the dynamic KAFO rather than in children being treated with the static KAFO

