#### Sample size calculation

Expecting a 5 degree change in ankle ROM (assumed as clinically relevant), with a standard deviation of 4.5 degrees, a significance level (α) of 0.05 that is corrected for comparisons between three groups using a Bonferroni correction (α = 0.0167), and a power level of 80%, 13 children in each group will be sufficient. The calculation takes five repeated measurements with a correlation coefficient of ρ = 0.7 into account. In this study, 66 participants (22 in each group) will be recruited to allow drop outs.

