### Statistics

Statistical analysis will be performed according to an "intention to treat" principle. All relevant subject characteristics, such as age, body weight and length, gender, clinical diagnosis, will be described by their mean value and standard deviation, or percentages. Differences between groups at baseline will be tested using linear regression techniques or Chi-square statistics. The effect of the intervention will be analysed using a multi-level analysis, with the primary and secondary outcome measures as dependent variables and treatment group and time as independent variables. To test for any differences in the changes of variables between groups, a treatment*time interaction is included as independent variable. Analysis are adjusted for treatment site (Amsterdam, Arnhem or St Louis). Covariates will be: 1) KAFO wearing time, 2) lower leg growth, 3) use of an AFO by day, 4) stretching exercises and 5) level of spasticity. The α-value will be set at 0.05.

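### The Statistics section sets alpha at 0.05 without carrying forward the Bonferroni level of 0.0167 on which the trial was sized, and does not say whether 0.05 is family-wise or per comparison

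*Protocol article*

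**What the plan says.** Three places in the protocol article bear on this.

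- **Sample size calculation.** The trial is sized with "a significance level (α) of 0.05 that is corrected for comparisons between three groups using a Bonferroni correction (α = 0.0167"). With the other stated inputs this leads to "a power level of 80%, 13 children in each group will be sufficient"; 22 per group are to be recruited to allow for dropout.
- **Hypotheses, Clinical part.** Children treated with a KAFO are expected to do better on ankle dorsiflexion than children without one. In addition, "children who are treated with a static KAFO will show less of a response" than those with a dynamic KAFO. The Background also makes the static-dynamic comparison an aim of the study.
- **Statistics.** A multi-level model with treatment group, time and their interaction is planned for the primary and secondary outcomes. The section closes with "The α-value will be set at 0.05". It names no pairwise contrast and no multiplicity procedure, and it does not refer back to the sample size section.

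**The concern.** One section pays for a per-comparison level of 0.0167, and the section that governs the analysis gives 0.05 without qualification. An analyst who follows the Statistics section could call a pairwise result with p = 0.03 significant; one who follows the sample size section could not. Every claim on the primary outcome depends on this threshold. If it stays open, it may be settled after the results are known.

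The interaction test does not settle the matter. A three-group interaction can show that the groups change differently, but not which KAFO differs from control or whether dynamic beats static. The hypotheses therefore need pairwise contrasts, and the level of those contrasts is what the document leaves unclear.

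**Working it through.** **Inputs.** From the Sample size calculation section: difference 5 degrees, SD 4.5 degrees, five measurements with correlation 0.7, power 80%, alpha 0.05/3 = 0.0167. Sidedness is not stated; two-sided is assumed because it reproduces the plan's figure (one-sided gives 10.9, so 11).

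**Step 1: reproduce the 13 per group.**

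n = 2 × [SD × (z(1−α/2) + z(0.80)) / difference]² × (1 + 4ρ)/5

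- Variance factor for the mean of five measurements: (1 + 4 × 0.7)/5 = 0.76.
- 2 × (4.5/5)² = 1.62.
- At α = 0.0167: (2.394 + 0.842)² = 10.47, so n = 1.62 × 10.47 × 0.76 = 12.89, rounded up to **13**, as stated.
- At α = 0.05: (1.960 + 0.842)² = 7.85, so n = 1.62 × 7.85 × 0.76 = 9.66, rounded up to **10**.

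With the repeated-measures factor that the plan says it used, 13 requires the corrected alpha. Without that factor, α = 0.05 also gives 13 (12.7), but then 0.0167 gives 17. The plan states both the correction and the repeated measurements, and together they give 13.

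**Step 2: family-wise error at the final analysis.** This is for one outcome and three equal arms with no true difference. The three contrasts share arms, so the exact figure comes from the studentized range for three means: P(range > √2 × z(1−α/2)). Simulation with 10⁶ draws of three arm means agrees.

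| Reading of the Statistics section | Family-wise error |
|---|---|
| Three pairwise contrasts, each at 0.05 | 12.2% (t-based: 12.0% at 13 and 12.1% at 22 per group) |
| Two KAFO-against-control contrasts, each at 0.05 | about 9.0% |
| Three pairwise contrasts, each at 0.0167 | 4.4% (t-based: 4.3%) |
| Global three-group test at 0.05, then pairwise at 0.05 only if significant | 5.0% |

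Treating the three contrasts as independent would give 1 − 0.95³ = 14.3%, which overstates the error because the contrasts share arms.

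**Step 3: power under each remedy, on the plan's own inputs.**

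- At 0.0167, power for a 5-degree difference is 80.4% with 13 per group and 96.7% with 22.
- With the gate, power for a 5-degree dynamic-against-control difference is 83% to 88% with 13 per group and 97% to 99% with 22, for a static-arm effect of 0, 2.5 or 5 degrees.

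These figures carry over the plan's model for the mean of five measurements. They are not an assessment of the power of the interaction test.

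**The case against.** The strongest reply is that the two sections agree. The sample size section also starts from 0.05 and derives 0.0167 from it, so the 0.05 in the Statistics section may be that same overall level, with the correction understood. The section also never says that each pairwise contrast is tested at 0.05. With three arms, the interaction can be read as one omnibus test, and if it gates the pairwise tests the error is about 5%. Further, the Hypotheses section spells out two comparisons (KAFO against none, static against dynamic); three pairwise contrasts are an inference, though one that the divisor of three supports. Finally, a condensed article may leave the mechanics of a correction to a fuller document.

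Much of this stands. A reader might infer that the trial has a 12% false-positive rate, or that the protocol prescribes unadjusted pairwise tests. The document supports neither: 12% applies under one permitted reading, and the other readings give about 9%, or 5% or less.

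The last argument does not remove the point. The article does not just omit a detail: it gives two levels and does not say how they relate. Neither benign reading is written down.

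**Conclusion.** The point holds as an unresolved inconsistency in the decision threshold for the primary outcome. The design uses 0.0167 per comparison; the analysis text gives 0.05 and leaves its meaning open. The family-wise error is about 12% if all three contrasts are tested at 0.05, about 9% if only the two against control are, and about 5% or less if the correction or a gate applies. These figures assume two-sided tests, equal arms and no true difference, and they cover the final analysis only.

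A reader might also infer that the sample size is wrong or that the trial is underpowered. The stated inputs reproduce 13 per group at the corrected level, so this inconsistency gives no reason to change it. Nor does holding each contrast at 0.0167 guarantee 5% for the trial as a whole: the section on premature termination plans significance comparisons once 30 children have six-month data, and that is a separate source of error.

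**What to change.** Add one sentence to the Statistics section, in one of two forms:

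1. For the primary outcome, 0.05 is the family-wise level, and each of the three pairwise contrasts (static against control, dynamic against control, dynamic against static) is tested at 0.0167. This matches the sample size directly.
2. The global three-group treatment-by-time test must be significant at 0.05 before any pairwise contrast is tested at 0.05. With exactly three groups this holds the family-wise error at 5%, provided the global test and the contrasts concern the same measure of change.

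The cost is the sentence. On the plan's own inputs, power stays at about 80% with 13 per group under the first form and is slightly higher under the second. The sample size does not change. How the interim comparison affects the error rate needs its own statement. Labelling the secondary outcomes as supportive is optional.

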## Discussion

This randomised controlled trial focuses on the efficacy of orthotic management in rest in children with CP to prevent a decline in ankle dorsiflexion at full knee extension. Although orthotic management in rest in children with CP is widely applied, very little is known about the efficacy of this treatment. Therefore, more research on the efficacy of orthotic management in rest is needed. We decided to focus on the efficacy of two types of KAFOs as orthotic management in rest treatment since we expect that KAFOs will be the most effective in preventing loss of ankle dorsiflexion range. This expectation is based on the fact that a KAFO, in contrast to an ankle-foot-orthosis (AFO), is able to impose both knee extension and ankle dorsiflexion simultaneously. This may lead to more stretch on the *Gastrocnemius muscle *which is the target muscle of this study. The *Gastrocnemius muscle *is often affected in children with spastic CP, having equines [9].

To measure the efficacy of orthotic management in rest, the ankle dorsiflexion has to be measured in a reliable and valid way. In order to achieve that, a custom designed hand held dynamometer [31] is used to measure the ankle dorsiflexion angle. The device allows reproducible measurements of the ankle angle-moment relationships [31]. This is important as ankle dorsiflexion depends on the exerted dorsiflexion moment. Standardization of this measurement procedure reduces variability of ankle moment and angle measurements and hence increases the sensitivity to measure changes in ROM. Furthermore, the device allows the investigator to correct for foot deformations by using two separate adjustable foot plates (to stabilize the talonavicular joint) [31]. Foot deformations like equinovarus and equinovalgus [44] can, if not corrected, affect the ankle dorsiflexion measurement results.

The custom designed hand held dynamometer also allows us to measure morphological parameters of the *medial Gastrocnemius muscle *at a standardized ankle position during repeated measurements. By measuring changes in the morphological parameters and changes in ankle ROM simultaneously, we will gain insights into the working mechanisms of orthotic management in rest. As described in the methodological section we obtain the morphological parameters by a 3D ultrasound method. We decided to use this method instead of a 2D ultrasound technique, because 3D ultrasound offers the advantage of measuring the morphological parameters in the mid-longitudinal fascicle plane. Previous research has shown that measuring outside of the mid-longitudinal fascicle plane leads to over or under estimation of the results [43].

The primary outcome measure of this study (ankle dorsiflexion ROM) is an impairment parameters at the body-function level of the International Classification of Function, disability and health (ICF) [45]. Improvements (or less decline) in this parameter do not necessarily lead to improvements in activity level of the ICF model, such as walking [45]). In order to better understand the impact of orthotic management during rest on activity level, this study will also investigate improvements in gait and gross motor function level in response to treatment.

In conclusion, this randomised controlled trial is aimed to provide insight in the efficacy of orthotic management in rest on body function level (ankle dorsiflexion range of motion) and activity level (gait, gross motor function), and will provide insight in the treatment's underlying myological adaptive mechanisms. The results of this study may provide indications for improved treatment strategies for children with cerebral palsy and in particular the use of orthoses.

## Abbreviations

CP: Cerebral Palsy; ROM: Range Of Motion; KAFO: Knee-Ankle-Foot Orthosis; *ℓ*_(fasc)_: Fascicle length; *ℓ*_m_: Muscle belly length; A_f_: Physiological cross- sectional area; *γ_(fasc)_*: Angle between fascicle and aponeurosis; *ℓ*_t_: Tendon length; AFOs: Ankle-Foot Orthoses; *γ_(f-t)_*: Angle between the footplate of the foot fixation and the tibia; EMG: Electromyography; MVC: Maximal Voluntary muscle Contraction; GMFM-66 IS: Electromyography; GMFCS: Gross Motor Function Classification System; AOC: Angle Of Catch; SCALE: Selective Control Assessment of the Lower Extremity; *ℓ*_(m th)_: Muscle thickness; *ℓ*_a_: Length of the aponeuroses; *ℓ*A_f_: Length component of the physiological cross-section; ICF: International Classification of Function, disability and health.
